## Abstract

**Background:**

Depressive disorders are a leading cause of disability among women worldwide, yet existing interventions often fail to account for the biological and sociocultural factors shaping women’s risk and symptom presentation.

**Objective:**

In response, this randomized, single-blind, controlled trial will evaluate the efficacy of the 3D Program—a gender-sensitive, guided internet-based cognitive behavioral therapy (iCBT) intervention for women with moderate depressive symptoms.

**Methods:**

A total of 120 women presenting with moderate depressive symptoms (17-item Hamilton Depression Rating Scale score 17‐23), aged 18 to 45 years, will be randomized to receive either the 10-week 3D Program or informational video content, with both groups continuing treatment as usual. The 3D Program will integrate personalized therapist support, self-guided digital modules, and a moderated online group, with content cocreated alongside women with lived experience of depressive symptoms. The primary outcome will be the change in depressive symptom severity, measured by the 17-item Hamilton Depression Rating Scale at 12- and 26-week postbaseline assessments. Secondary outcomes will include functioning, quality of life, perceived stress, and menstrual-related distress. Additionally, the study will explore potential biological predictors of treatment response, analyzing metabolic markers related to tryptophan metabolism and adrenal steroid pathways across multiple biological matrices. Data analyses will use linear mixed-effects models and multivariate techniques to examine treatment effects and possible biomarker associations.

**Results:**

The trial was funded in October 2023 (grant PI23/00257, Spanish Ministry of Economy and Competitiveness), and ethical approval was obtained in February 2024. The trial was registered in July 2025 (ClinicalTrials.gov NCT07060690). Data collection began in March 2026 and is projected to conclude in August 2027. As of April 2026, a total of 8 participants have been enrolled. Data analysis has not yet commenced. The results are expected to be published in the summer of 2028.

**Conclusions:**

This trial aims to address critical gaps in accessible, personalized, and gender-sensitive mental health care. If effective, the 3D Program may serve as a scalable, cost-efficient adjunct to routine care for women with depressive symptoms in public health systems, while biomarker findings may lay the groundwork for future trials examining predictors of response.

## Introduction

Depressive disorders are consistently more prevalent among women than men worldwide [1], with depression ranking as the 6th and 13th leading cause of disability in women and men, respectively [2]. In Spain specifically, depression affects women at twice the rate of men [3]. Women also face sex- and gender-specific risk factors, including hormone-related depressive disorders—premenstrual dysphoric disorder, peripartum depression, and perimenopausal depression—and sociocultural stressors such as higher exposure to interpersonal stress, caregiving responsibilities, and gender-based discrimination [4-7].

Even when depression is detected, many individuals do not receive evidence-based treatments considered minimally adequate [8,9], due to limited access, structural deficiencies, social stigma, and cost barriers—challenges present not only in low- and middle-income countries but also in high-income settings such as Spain [10]. Among psychological treatments for depression, cognitive behavioral therapy (CBT) is the most widely studied globally and consistently recommended as a first-line psychological treatment in Spain [11,12]. Internet-based CBT (iCBT) has emerged as a scalable alternative, demonstrating comparable effectiveness to face-to-face therapy for mild-to-moderate depression when guided by human support [13]. However, digital interventions face significant challenges, such as low adherence and lack of personalization, which reduce both engagement and effectiveness [14,15].

This one-size-fits-all approach is especially problematic for women, whose depression is shaped by unique biological and sociocultural risk factors rarely addressed by current approaches [7,16]. Addressing these sex- and gender-related differences may require insights from emerging biological research [17]. Two metabolic pathways—tryptophan metabolism and adrenal steroidogenesis—show promise for understanding the biological contributors to depression and informing personalized treatment approaches. Inflammatory processes can shift tryptophan metabolism from serotonin production toward the kynurenine pathway, a mechanism linked to depressive symptoms [18,19]. Adrenal steroidogenesis, which regulates the stress response and produces corticosteroids and sex hormone precursors, shows dysregulation patterns implicated in sex differences in depression [20].

To address persistent gaps in accessible, personalized, and gender-sensitive mental health care, this study will conduct a randomized controlled trial (RCT) evaluating the efficacy of the 3D Program, a gender-sensitive, guided iCBT intervention for women with moderate depressive symptoms, which was cocreated with multidisciplinary experts and women with lived experiences. We hypothesize that participants receiving the 3D Program will experience greater reductions in depressive symptoms compared to controls. Additionally, we will explore metabolic biomarkers related to tryptophan and steroid pathways in relation to treatment response.

## Methods

### Study Design

This study is a randomized, single-blind, parallel-group, controlled trial testing the efficacy of the 3D Program—a gender-sensitive, guided iCBT intervention for women with moderate depressive symptoms delivered over 10 weeks compared to informational videos. The study outline is presented in Figure 1, and Checklist 1 contains the SPIRIT (Standard Protocol Items: Recommendations for Interventional Trials) checklist, as this protocol was developed in accordance with the SPIRIT guidelines [21].

**Figure 1. F1:**
[figure not shown]
Flowchart of the study design*.* RCT: randomized controlled trial; TAU: treatment as usual.

The study encompasses 2 components: first, an evaluation of the intervention’s efficacy, and second, an exploratory investigation of metabolic signatures associated with treatment response, focusing on tryptophan and steroid-related pathways.

### Study Setting

#### Overview

Participants will be recruited from outpatient and community services within Hospital del Mar (Barcelona, Spain). The intervention will be delivered fully online: participants will engage with the program at home, while the therapists will conduct individual sessions from Hospital del Mar facilities to ensure privacy and compliance with ethical standards.

#### Patient and Public Involvement

The 3D Program was refined through a 2-phase cocreation and coadaptive process. Phase 1 involved a multidisciplinary panel of women (n=6; including a psychiatrist, a gynecologist, a medical doctor, and 3 psychologists) who developed the 10 self-guided modules. In phase 2, a total of 8 women with lived experience of depressive symptoms were recruited from existing research databases to participate in five 120-minute workshops. Using creative participatory dynamics, these sessions served to adapt the intervention content and test the beta platform, ensuring the clinical relevance, acceptability, and usability of the 3D Program.

### Participants

#### Recruitment

Recruitment will take place over a 12-month period and will conclude once the target sample size (N=120) is reached or the recruitment period ends, whichever occurs first. Recruitment strategies will include (1) attending regular clinical meetings; (2) displaying posters with a brief overview of the study in common areas of the hospital, as well as local libraries, civic centers, and university campuses within the Hospital del Mar catchment area; and (3) maintaining close contact with clinicians across inpatient, outpatient, and primary care settings to increase awareness of the study.

All participants meeting the inclusion criteria will be invited to participate by their treating clinical teams. If referred by nonmental health professionals, participants will be screened by a study psychologist or psychiatrist to confirm the presence and severity of depressive symptoms.

#### Eligibility

Eligible participants will be women (including both cisgender and transgender) aged 18 to 45 years (inclusive) who present with moderate depressive symptoms at baseline, defined as a score of 17 to 23 on the 17-item Hamilton Depression Rating Scale (HDRS-17). Additional inclusion criteria are fluency in Catalan or Spanish, regular internet access, and the ability to independently use a digital device (eg, smartphone, tablet, or computer).

Participants will be excluded if they are currently receiving psychological therapy, as concurrent structured psychotherapy would confound the estimation of the 3D Program’s effect; have participated in another interventional clinical trial for depression in the past 3 months; are pregnant or planning to become pregnant during the study period, given the distinctiveness of perinatal depression and because pregnancy-related hormonal fluctuations would confound the exploratory biomarker analyses; have cognitive impairment that would interfere with informed consent or study participation; or currently present with psychotic symptoms, active suicidal ideation, or substance use disorder. Women older than 45 years will be excluded to minimize potential confounding effects of perimenopausal hormonal changes. Participants with severe depression will be excluded due to safety considerations, as this population requires more intensive, closely monitored treatment than the 3D Program is designed to provide.

### Intervention

#### Experimental Group

Participants in the experimental group will receive the 3D Program—a gender-sensitive, guided iCBT intervention for women with depressive symptoms—delivered over 10 weeks alongside treatment as usual (TAU).

The 3D Program comprises 10 weekly self-guided modules, accessed via a secure website, incorporating video content, written materials, and interactive activities such as worksheets. Topics cover issues commonly experienced by women, including hormonal changes, caregiving, body image, and experiences of sexism. Prior to beginning the program, participants will receive an orientation video on how to navigate the platform.

In addition to the self-guided modules, participants will receive 6 individual online sessions with a trained female psychologist. The intervention adopts a personalized approach, allowing therapists to tailor each participant’s module sequence based on individual needs and clinical relevance. All therapists will complete training focused on the 3D Program and the principles of online psychological support.

Participants will also have access to an online peer support group, moderated by a trained female facilitator who will guide discussions to foster connection and safety. The group aims to reduce isolation, promote shared experiences, and challenge maladaptive beliefs such as “this only happens to me.”

The module content and group space were cocreated and coadapted through 5 workshop sessions with women with lived experience of depressive symptoms. Details on the content of the 3D Program modules are presented in Table S1 in Multimedia Appendix 1.

#### Control Group

Participants in the control group will receive 6 short informational video capsules based on selected content from the 3D Program modules in addition to TAU. Details on the content can be found in Table S2 in Multimedia Appendix 1.

To ensure an even distribution of content over the 10-week period, participants will be given access to 1 video every 14 days, facilitating regular engagement and structured exposure to the material. Control group participants will not receive interactive tasks or one-to-one sessions with a therapist.

All participants, regardless of group allocation, will continue their TAU under the supervision of their clinical care team. TAU comprises standard Spanish National Health System care, involving primary care coordination and specialist referrals to mental health services as needed. This encompasses psychoeducation, symptom monitoring, and first-line pharmacotherapy with selective serotonin reuptake inhibitors, plus short-term benzodiazepines if needed. Brief psychological interventions (eg, CBT) or more intensive psychotherapy may be provided for mild-moderate cases if indicated [12]. However, individuals currently receiving any such active treatment will be excluded from this trial to avoid potential confounding effects. No modifications to ongoing clinical care will be made for research purposes, ensuring that the 3D Program serves as a naturalistic adjunct to standard treatment.

#### Criteria for Discontinuing or Modifying Allocated Interventions

Participants may withdraw from the study at any point without providing a reason. The research team may also discontinue a participant’s involvement if continuation poses a risk to their well-being, or if significant protocol deviations occur (eg, inability to engage in the intervention as intended). Discontinuation may also occur in consultation with the treating clinical staff if significant clinical symptoms emerge that require alternative or intensified care, in which case participants will be referred to an appropriate service.

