#### Relevant Concomitant Care Permitted or Prohibited During the Trial

Pharmacological treatment will be permitted, provided it was initiated at least 1 month before study entry. Concomitant pharmacotherapy (agent and dose) will be recorded at baseline, tracked for changes during subsequent assessments, and compared between the groups after randomization to detect any imbalances. Any concurrent psychological interventions or psychological care will not be permitted during the trial period to avoid confounding effects. Should any intensification of clinical care become necessary during the trial—including psychological interventions, changes to pharmacotherapy, specialist referrals, or crisis interventions—it will be documented in the trial log as part of the adverse event monitoring procedure. Where these intensifications reflect clinically significant symptoms worsening requiring alternate or intensive care, the participant may be discontinued from the trial in consultation with their treating team (see the *Criteria for Discontinuing or Modifying Allocated Interventions* section).

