#### Procedure

Assessments will be conducted at 3 time points: baseline (T0), postintervention (12 weeks after baseline, T1), and follow-up (26 weeks after baseline, T2).

The baseline assessment will include the collection of sociodemographic and clinical data, the administration of primary and secondary outcome measures, a gynecological consultation to assess hormonal and menstrual health, and the collection of biological samples.

At T1 and T2, follow-up assessments will include the administration of primary and secondary outcome measures as well as biological sample collection.

All psychological assessments will be carried out by a trained professional (psychologist, physician, psychiatrist, or psychiatric nurse), gynecological examinations will be performed by a licensed gynecologist (MD in obstetrics and gynecology), and biological samples will be collected by a registered nurse. Participant timeline, including the schedule of enrollment, interventions, and assessments, is outlined in Table 1. All professionals with direct participant contact—whether via teleconference or in-person—will be women. This decision was reached by consensus within the focus group of women with a lived experience of depression, who expressed that sensitive topics (eg, hormonal changes, gender discrimination, and sexuality in the context of depression) would be better understood by female professionals and that participants would feel more comfortable accordingly.

**Table 1. T1:** SPIRIT (Standard Protocol Items: Recommendations for Interventional Trials) participant timeline.

Study procedure	Trial period					
	Preintervention			Intervention	Postintervention	Follow-up
Time point	–t0	T0	T0	—^a^	T1	T2
Weeks	0	1	2	3‐12	12	26
Enrollment						
Eligibility screen	*✓*					
Informed consent		✓				
Inclusion		✓				
Randomization		✓				
Interventions						
Intervention (3D Program)				✓		
Control group (informational videos)				✓		
Screening assessments						
Sociodemographic information		✓				
Medical and psychiatric history		✓				
Gynecological visit			✓			
Primary outcome						
HDRS-17^b^		✓			✓	✓
Secondary outcomes						
WHODAS 2.0^c^		✓			✓	✓
EQ-5D-5L^d^		✓			✓	✓
PSS^e^** **		✓			✓	✓
MEDI-Q^f^** **		✓			✓	✓
Biological samples						
Plasma			✓		✓	✓
Saliva			✓		✓	✓
Urine			✓		✓	✓
Nails			✓		✓	✓
Hair			✓		✓	✓

a Not applicable.

b HDRS-17: 17-item Hamilton Depression Rating Scale.

c WHODAS 2.0: World Health Organization Disability Assessment Schedule 2.0 (36-item version).

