#### Outcome Analysis and Longitudinal Modeling

Primary and secondary outcomes will be analyzed using an intention-to-treat (ITT) approach, with all participants analyzed according to their original randomization group. Linear mixed-effects models (LMMs) will be used to examine changes over time and between groups for the HDRS-17, WHODAS 2.0, EQ-5D-5L, PSS, and MEDI-Q scores. These models will include fixed effects for group, time, and their interaction, with a random intercept for participants to account for within-subject correlation over time.

While change scores may be calculated for descriptive or interpretative purposes, the LMMs will serve as the primary inferential approach. In the event of a significant group × time interaction, post hoc simple effect analyses will be conducted to evaluate between-group differences at a specific time point and within-group changes from baseline, using estimated marginal means with appropriate corrections for multiple comparisons.

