#### Missing Data

Following the ITT principle, LMMs will be applied without imputation, as they appropriately handle missing data under the missing at random assumption, and imputation may introduce unnecessary bias. Cluster and factor analyses will also be conducted without imputation, as they rely solely on baseline data, assuming that missingness is minimal and not systematic. Multiple imputation will be performed only for analyses that require it, such as multiple regression models and partial least squares regression.

All analyses will be 2-tailed, with statistical significance set at *P*<.05.

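### The discontinuation rules can end a woman's participation in the trial, not only her intervention, for non-engagement or worsening, which undermines the intention-to-treat approach and the missing-at-random assumption

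*Protocol article*

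**What the plan says.** The section on criteria for discontinuing or modifying allocated interventions is headed as a rule about the intervention, but its text goes further: "The research team may also discontinue a participant’s involvement if continuation poses a risk to their well-being, or if significant protocol deviations occur". The example it gives of such a deviation is non-engagement: "significant protocol deviations occur (eg, inability to engage in the intervention as intended". It adds that discontinuation may follow, in consultation with clinical staff, when symptoms need other or more intensive care.

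The section on concomitant care refers back to that rule and names the trial as what is left: where intensified care reflects clinically significant worsening, "the participant may be discontinued from the trial in consultation with their treating team".

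The analysis sections assume that outcomes are available, or are missing for ignorable reasons. Outcome Analysis and Longitudinal Modeling specifies intention to treat, "with all participants analyzed according to their original randomization group", and describes the model: "These models will include fixed effects for group, time, and their interaction, with a random intercept for participants". Missing Data states that "LMMs will be applied without imputation, as they appropriately handle missing data under the missing at random assumption". The Discussion cites the intention-to-treat analysis and the attrition allowance as mitigation for its concern about selection and dropout.

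On timing, the Procedure section states: "Assessments will be conducted at 3 time points: baseline (T0), postintervention (12 weeks after baseline, T1), and follow-up (26 weeks after baseline, T2". Table 1 shows no HDRS-17 between baseline and T1.

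**The concern.** Stopping an intervention and leaving a trial are different events. Intention to treat needs the outcome of every randomized woman, including those who did not engage or who got worse. The rules as written do not separate the two events, and no section says that T1 and T2 are still assessed after the intervention ends.

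The two stated grounds, inability to engage and worsening, are adherence and a close relative of the outcome itself. Neither is in the primary model. If removal depends on a course that no HDRS-17 visit has recorded, the missing-at-random assumption fails. If it also acts differently in the two arms, the estimated effect is biased.

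The arms do differ in exposure to the rule. The Adverse Events section has therapists look for worsening during individual sessions. The Control Group section says that controls have no one-to-one sessions and no interactive tasks. The therapists are unblinded, and the rule is discretionary.

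**Working it through.** **1. The plan's own sample size.** Inputs from Sample Size Calculation: f = 0.15, α = 0.05, power 0.90, 2 groups, 3 measurements, correlation ρ = 0.5, ε = 1. For the within-between interaction, λ = f² × N × m × ε / (1 − ρ) = 0.0225 × 96 × 3 / 0.5 = 12.96, with df1 = 2 and df2 = (96 − 2) × 2 = 188. Power is 0.902 at N = 96 and 0.896 at N = 94, so 96 is the smallest even N that reaches 0.90. Attrition: 96 / (1 − 0.20) = 120. Both stated figures reproduce, and the point does not touch them.

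**2. What a removed woman leaves behind.** HDRS-17 is taken at T0, T1 and T2 only. A woman removed before T1 contributes one score, which eligibility restricts to 17-23. Given that score, group and time, the model predicts her T1 and T2 as if she were like the women who stayed.

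**3. Size under stated assumptions.** Simulation: 60 per arm, no true effect, scores in SD units, ρ = 0.5, 1,500 trials per scenario. Analysis: group × time on all available data with compound symmetry, which corresponds to the planned random-intercept model (ρ held at its true value), tested with the two-sided 2-df interaction test. Removal deletes T1 and T2. It is driven by the unobserved change from T0 to T1, either exactly or with added noise of 1 SD; the ranges span these two versions. Negative values favor the program.

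| Removed, experimental / control | Bias at T1 (SD) | Type I error |
|---|---|---|
| 5% / 0% (3 women) | −0.06 to −0.08 | 5-6% |
| 10% / 0% (6 women) | −0.10 to −0.14 | 7-10% |
| 20% / 0% (12 women) | −0.18 to −0.26 | 13-21% |
| 15% / 5% (9 and 3 women) | −0.09 to −0.12 | 7-9% |
| 10% / 10% or 20% / 20% | within 0.01 | 4-5% |

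Bias at T2 in the unequal scenarios is smaller, 0.03 to 0.09 SD. When removal is random or depends only on baseline HDRS-17, T1 bias stays within about 0.01 SD and type I error is 4.5-5.7%. The damage therefore comes from the mechanism, not from the loss itself. The simulation error of a 5% rate with 1,500 trials is √(0.05 × 0.95 / 1,500) = 0.6 percentage points, so the first row is hardly distinguishable from nominal.

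**4. Scale.** If f = 0.15 stands for an equal difference d at T1 and T2 and none at T0, then f = d / √18 and d = 0.15 × 4.243 = 0.64 SD. The T1 bias is then 16-22% of the design effect at 10% removed (0.10 / 0.64 to 0.14 / 0.64) and 28-41% at 20% removed (0.18 / 0.64 to 0.26 / 0.64).

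**The case against.** A reader might infer that the rules contradict intention to treat, that removal will fall mainly on the experimental arm, and that the program will therefore look better than it is. The documents do not support any of these in that form.

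- **Contradiction.** No section says that removed women leave the analysis. The mixed model keeps whatever they have contributed, in the arm to which they were randomized. What is lost is follow-up, so intention to treat is undermined rather than contradicted.
- **Failure of missing at random.** This depends on why women are removed. The example given is inability to engage, and nothing in the document shows that it tracks severity. Removal related only to recorded scores would leave the model valid.
- **Unequal removal and direction.** Both arms stay under their clinical teams, symptom monitoring is part of usual care, and the rule on intensified care applies to everyone. If controls, who have no therapist, worsened more and were removed, the bias would run against the program. The extra detection route in the experimental arm makes a difference possible, not certain.
- **Rates.** The document gives only 20% overall attrition and says that removal may happen. Every removal rate above is an assumption.
- **Condensation.** This is an article, and the full protocol may say that assessments continue. Sensitivity analyses may be in an unseen analysis plan, and their absence is not held against the trial.

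These points limit the size of the concern, but they do not remove it. The article is not merely silent: it states a rule that ends involvement and, in one section, names the trial as what is left. An analysis plan cannot recover visits that were never made.

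**Conclusion.** The point holds as a defect in a stated rule. Followed as written, the two discontinuation sections can cost primary outcomes for reasons tied to adherence or to the outcome, and the planned model has little with which to correct for that.

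The consequence may be nil (equal removal, or removal that depends only on recorded scores), small (type I error of 5-6% at 5% one-arm removal) or material (13-21% at 20%). The larger figures need removal that is driven by unobserved worsening and confined to the experimental arm. They also assume no other attrition and a correlation of 0.5 even though eligibility narrows the baseline range. They illustrate what could happen and do not forecast this trial. It is still worth settling now: 8 women were enrolled as of April 2026, and outcomes that are not collected cannot be recovered.

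**What to change.** Reconcile the sections on discontinuation criteria and concomitant care with those on outcome analysis and missing data:

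- Separate discontinuation of the allocated intervention from the end of follow-up.
- State that T1 and T2 outcome assessments continue for every randomized woman unless she withdraws consent to follow-up.
- Record non-engagement as adherence, and do not use it as a ground for ending outcome assessment.

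When an intervention is stopped or care is intensified remains a clinical decision, and this change does not touch it. If the full protocol already provides for continued assessment, only the wording needs to be aligned.

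The cost is a short amendment, notified to participants, the ethics committee, the registry and investigators as the Protocol Amendments section requires, plus some effort to assess women who have stopped the intervention. The visits are already in Table 1, and the sample size stays at 120.
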